### MLMs

Predictive MLMs for classification and regression will be designed, trained, and tested following the methodology outlined by Luo and colleagues [77] in their Guidelines for Developing and Reporting Machine Learning Predictive Models in Biomedical Research.

### Data Preprocessing

Databases and labeling will initially be managed using Microsoft Excel (version 2412), after which MATLAB (version 2025a, MathWorks, Inc) will be used for data preprocessing. This process will include data cleaning and preparation to ensure the dataset is suitable for ML training.

Feature selection will be done following a filter methodology after correlation analysis to assess the correlation with the target and statistical measures. All data obtained through the wearable device, psychological assessment and ESDC will be scaled through a *z*-score standardization for dimensionality reduction and integration across all modality.

The data will be divided into training, validation, and test datasets using a k-fold cross-validation approach. The dataset will be split into k folds, with 2 folds randomly selected: one for validation and another for testing. The remaining k-2 folds will be used for training. The number of folds will vary depending on the specific model, enabling a broader experimental variance and improved model evaluation.

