### Participant Identification and Randomization

Participants in both groups will be randomly assigned a unique identification number, which will be used throughout the study to ensure anonymity and meet the inclusion criterion of randomization. Psychological assessments conducted at the rehabilitation center will be conducted through self-reported questionnaires, administered in a traditional pen-and-paper format, overseen by the institution’s psychologists, who will use only the assigned ID numbers during the digitization of all data. Control participants will complete all psychological tests in a self-reported computer-based format, using their ID numbers, which will be randomly assigned at the start of the monitoring period.

A secondary randomization process will be conducted to create k-clusters of data before training the ML algorithm. This step will also include the selection of test data for verification purposes, ensuring robust validation of the model.

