### Statistical Analysis

Statistical analysis will be conducted using R-Studio IDE (version 4.3.1; Posit PBC), Prism GraphPad (version 9, GraphPad Software Inc), and MATLAB (version R2025a, MathWorks Inc). A descriptive analysis of normality (Shapiro-Wilkin normality test) means and medians, SD and error, variance (ANOVA or Kruskal-Wallis tests) will be performed. Correlation analyses (Spearman or Pearson) will be conducted to gain a preliminary understanding of the interactions between variables, as well as using time series analysis descriptive models to identify patterns, trends and cycles of activities by participants, and by groups. MATLAB will be used for advanced data processing and visualization, ensuring robust and comprehensive analysis.

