### Data Exclusion

Missing data will be addressed through imputation. If more than 20% of daily data samples are missing, they will be excluded. For missing data below this threshold, linear interpolation and neighbor mean imputation (k-nearest neighbor) will be applied during preprocessing using MATLAB.

The quality of data collected from the smart band will be assessed by correlating heart rate at randomly selected timestamps with oxygen saturation, activity levels, self-reported exercise, and sleep type during sleep hours. If atypical correlations are identified, 10 data points before and after the anomaly, along with 5 additional randomly chosen timestamps, will be reviewed. A day with more than 20% of faulty measurements will be excluded from the dataset.

Data will also be excluded in cases of device misuse, such as exchanging the device with other participants or nonparticipants, switching the wearing side without prior notice, or removing the device for more than 5 hours without informing the research team.

If the total sum of missing and excluded data exceeds 20% of the 6-month period, the participant's data will be removed from the study. Finally, for SUD participants, any measurements obtained during periods of substance use will be excluded, and their participation in the study will be terminated.

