### Outcomes

#### Profiles

A total of 4 distinct subprofiles will be generated based on the results of the statistical analysis: (1) demographic, (2) psychological, (3) craving, and (4) digital biomarkers. These profiles will subsequently be integrated to create digital phenotypes for individuals with SUD.

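### The feature filter uses the outcome label, is described before the split into folds and is not confined to training data, so the test AUC that decides success would be biased upwards

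*Protocol article*

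**What the plan says.** Data Preprocessing in the protocol article describes three steps in this order:

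1. **A filter on the outcome:** "Feature selection will be done following a filter methodology after correlation analysis to assess the correlation with the target and statistical measures".
2. **Scaling:** "All data obtained through the wearable device, psychological assessment and ESDC will be scaled through a" z-score standardization.
3. **The split:** "The dataset will be split into k folds, with 2 folds randomly selected: one for validation and another for testing". The other k−2 folds are for training. The section adds: "The number of folds will vary depending on the specific model".

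Other sections bear on the timing:

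- **Participant Identification and Randomization** places the creation of the folds relative to training only: "A secondary randomization process will be conducted to create k-clusters of data before training the ML algorithm".
- **Statistical Analysis** plans correlations with no restriction to training data: "Correlation analyses (Spearman or Pearson) will be conducted to gain a preliminary understanding of the interactions between variables".
- **Data Exclusion** says that "linear interpolation and neighbor mean imputation (k-nearest neighbor) will be applied during preprocessing using MATLAB". It names neither the donor set nor the order relative to the folds.

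Validation and Verification reads the final AUC and F2 from the test dataset and sets the mark at AUC ≥0.80 and F2 ≥0.8. The Predictive Model section repeats both. The abstract gives AUC alone as the condition for building the clinical interface.

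**The concern.** A filter that ranks features by their correlation with the target is part of model fitting. If it is run on everyone, the test participants' labels have already influenced which features enter the model, and the test fold is no longer independent. With few participants and many candidates, some features correlate with the label by chance. They do so in the test participants too, because those participants helped to select them.

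The test AUC is the figure on which the model is to be judged functional and an interface for clinical use built. If it is inflated, the plan's last safeguard against a useless model is weakened.

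A second, separate issue concerns the comparison of algorithms. Algorithms and Validation and Verification compare neural networks, trees, random forests and support vector machines. If k differs between them, they are trained on different shares of the data and scored on different test sets.

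**Working it through.** The plan states no expected AUC and no chance distribution for it, so there is no figure to reproduce. The question is what the described order does when there is nothing to predict.

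**Inputs from the article**
- At least 25 participants per group (Sample Size). This gives 25 SUD participants for the rehabilitation and relapse labels, and 50 for SUD against control.
- A relapse rate of 60% (Introduction), so 25 SUD participants split 15/10. The 50 are split 25/25.
- One fold for testing, one for validation and k−2 for training.

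**Assumptions, not in the article**
- 30, 60 or 120 candidate features. For scale, Table 2 alone lists 17 or 18 derived activity, heart-rate and sleep features, before rhythm, oxygenation, stress, demographics, eight instruments and the craving test.
- 5 or 10 features kept, k = 5, a two-class label, independent normal noise features and a ridge linear classifier.

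**Method.** Each setting used 1,000 simulated data sets (500 for AUC and F2 jointly, 200 for imputation). The features with the largest absolute correlation with the label were chosen either on all data or inside the training folds only. Fold-averaged means averaged over the five rotations of the test fold.

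**Filter on all data, pure noise**

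| Participants | Candidates | Mean test AUC | Fold-averaged AUC ≥0.80 | Single test fold ≥0.80 |
|---|---|---|---|---|
| 25 | 30 | 0.71–0.77 | 29–47% | 47–57% |
| 25 | 60 | 0.80–0.83 | 57–70% | 64–70% |
| 25 | 120 | 0.87–0.88 | 81–86% | 78–80% |
| 50 | 30 | 0.67–0.71 | 8–10% | 27–38% |
| 50 | 60 | 0.75–0.76 | 30% | 46–50% |
| 50 | 120 | 0.80–0.81 | 55–61% | 57–65% |

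**Filter inside training folds.** Mean AUC is 0.49–0.50. The fold-averaged AUC reaches 0.80 in 1.5–4.3% of runs (n = 25) and 0–0.2% (n = 50).

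**Both criteria together (10 kept; 30, 60, 120 candidates), filter on all data**
- n = 25: 9%, 16%, 22% fold-averaged; 29%, 40%, 41% on one fold.
- n = 50: 3%, 13%, 26% fold-averaged; 23%, 39%, 49% on one fold.
- With the filter inside training folds, the fold-averaged rates are 0.4–1.0% (n = 25) and 0–0.2% (n = 50).

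F2 alone is a weak guard. F2 = 5TP/(5TP + 4FN + FP), so calling everyone positive at prevalence π gives 5π/(4π + 1). At π = 0.60 this is 3.0/3.4 = 0.88. It reaches 0.8 once π ≥ 0.8/1.8 = 44.4%.

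**Scaling and imputation on all data, each tested alone.** Z-scoring gives mean AUC 0.50. k-nearest-neighbour imputation gives 0.49–0.50. Neither uses the label.

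**Test-fold size, no leakage.** With n = 25 and k = 5, a test fold holds 3 relapsers and 2 others, so there are 6 pairs, and AUC ≥0.80 needs at least 5 of them in the right order. Of the 10 equally likely rankings, 2 qualify: 20%. The simulation gives 17–21%. With 5 against 5 (n = 50), 19 of 252 rankings qualify: 7.5%. The simulation gives 7–8%.

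**Larger samples (60 candidates, 10 kept, filter on all data).** Mean AUC is 0.70 at n = 100 and 0.61 at n = 400.

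**Varying k.** Training uses (k−2)/k of the data. As an illustration with 25 participants, k = 5 leaves 15 for training and 5 for testing; k = 10 leaves 20 for training and 2 or 3 for testing.

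**The case against.** **The order is inferred.** No sentence says that the filter precedes the split. The split is itself described within Data Preprocessing, and a condensed article may leave fold-level detail to a fuller document. The plan also commits to a published guideline on machine learning models, whose content is not shown. This stands as a limit on certainty. Still, the article itself fixes the filter, its use of the target and the split, in that sequence, and nothing points to a training-only filter.

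**A reader might infer that all three steps leak.** The documents do not support that. The place of imputation relative to the folds is not stated, interpolation within one participant's series crosses no fold, and scaling and imputation on all data showed no measurable optimism. The target-based filter alone carries the effect.

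**A reader might infer that noise would usually be declared a success.** At 25 participants with 60 or more candidates, that is true of AUC alone. The success mark in the body of the article also requires F2, which brings the fold-averaged rate down to 3–26%. Part of the single-fold rate comes from tiny test folds and would remain without any leak.

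**The inputs are assumed.** Ridge is not among the planned algorithms, real features are correlated, the plan has a two-class and a three-class layer, and 25 per group is a floor. Sample Size counts only four independent variables, the profiles; if only those four entered, a filter would have little to choose from. But the Profiles section says "A total of 4 distinct subprofiles will be generated based on the results of the statistical analysis", and Data Preprocessing filters features, so more than four candidates is the natural reading. These points affect the size of the bias, not its direction.

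**The fold count may vary only within an algorithm.** The text says model, not algorithm. The comparison is therefore impaired only where k differs between algorithms.

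**Conclusion.** The point holds for the filter. As written, the plan describes selecting features on the target before dividing the data and does not restrict that step to training folds. Followed in that order, it makes the test AUC optimistic. Under the stated assumptions, noise features give a mean test AUC 0.2 to 0.4 above the chance value of 0.50 at the planned minimum of 25 SUD participants, and 0.17 to 0.31 above it with 50. The bias grows with the number of candidates and shrinks with the number of participants.

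It does not follow that the plan states this order outright, that scaling or imputation inflates the result, or that a worthless model would usually pass both criteria. The varying number of folds is explicit in the article. Its effect on the comparison of algorithms is conditional and has not been quantified.

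**What to change.** Replace the description in Data Preprocessing with a fixed order:

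1. Split by participant before any step that uses the outcome.
2. Within each training set only, fit the target-correlation filter and tune the hyperparameters. For good order, estimate the z-score parameters and the k-nearest-neighbour imputation there too. Apply all of them unchanged to the held-out folds.
3. Fix one k and use identical folds for every algorithm.
4. Compute the final AUC and F2 on pooled out-of-fold predictions from all participants, not on one small test fold. This addresses the chance passes that remain without leakage.

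The cost is a little more code, one revised paragraph and a lower reported AUC. No data collection changes. The Results section reports data already being labelled and preprocessed in June 2025, so the order should be settled before features are selected.

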### Blinding

Due to the nature of this study, neither the participants nor the first group of research staff will be blinded to group assignments. However, the group allocation of participant ID clusters will remain concealed from the second group of researchers. This second group will be responsible for data management, training the ML algorithm with the predictive model, and conducting validation, verification, and testing of the highest-performing models.

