### Timeline

This study will include 2 types of observations: continuous passive monitoring and active surveys conducted at specific time points. Passive monitoring will occur continuously for 6 months in both groups, followed by an additional year for participants with SUD after their discharge from the treatment facility. Active surveys will be conducted at three time points: (1) baseline session or baseline, (2) 3 months after baseline, and (3) 6 months after baseline.

For digital monitoring purposes, smart bands provided to participants will be synchronized with a smartphone at the baseline session. Psychological assessment will be conducted within the first 15 days after baseline. Retesting will take place during the 15 days prior to the 6 months after baseline. Emotional reactions to cravings will be assessed at two points: (1) 3 months after baseline and (2) at 6 months after baseline (Figures 1A-1F).

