### Validation and Verification

All models and algorithms will undergo validation, verification, and testing using MATLAB’s tools for model evaluation and hyperparameter optimization. These processes will assess precision, performance, and recall metrics. Optimal model performance will be defined by achieving an area under the curve (AUC) of ≥0.80 and F2 score of ≥0.8.

The output categories will serve as benchmarks to evaluate the validity, reliability, and precision of the models. The validation dataset will be used to perform initial comparisons both within individual models of each algorithm and across different algorithms, replicating models with distinct architectures to refine performance.

For model verification, the test dataset will be used to determine final AUC and F2 scores. This final evaluation will confirm the models’ effectiveness as ML tools for predicting rehabilitation outcomes and informing clinical decision-making.

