### Limitations and Considerations

This study is subject to several limitations and potential risks of bias that must be acknowledged. Participants will be selected through convenience sampling of patients with SUD in a rehabilitation facility, limiting participation to cisgender male individuals between 18 and 59 years of age in both groups, therefore limiting the generalizability of results. The experimental status will be disclosed to them beforehand as well. This awareness could influence self-reporting in psychological tests and responses during exposure to visual stimuli related to substance use, potentially introducing bias.

While the Xiaomi Redmi Smart Band 8 has been selected for its cost efficiency and suitability for future clinical applications in rehabilitation centers, its sensors may have higher measurement errors compared to research-grade devices. Studies have indicated that similar consumer-grade devices generally exhibit lower precision. However, this trade-off is justified by the need to prioritize accessibility and scalability in clinical settings.

To identify events of physical activity, such as exercise, and atypical behavior, this study will rely in self-reporting through the app included in the Xiaomi Smart Band 8 device in the control group. Activity of participants with SUD will also be assessed by classifying their behavior according to the fixed schedule at the rehabilitation facility. Data will be clustered time-wise according to the time of the day and the reported activity accordingly, to reduce possible noise created by this variability. Since these events will rely on self-reported activities, a margin of error might be present in the observations in this time window.

Data clustering by groups before final testing introduces a potential risk that research staff may infer group assignments prematurely, which could influence the interpretation of results. The reliability of data used for training the models also depends on participants’ proper use of the device and the accuracy of self-reported information, both of which carry inherent risks of bias that may impact outcomes.

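### The k-fold split does not make the participant its unit, so as written it permits one man's repeated records to fall in both training and test data

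*Protocol article*

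**What the plan says.** All references are to the protocol article.

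- **Data Preprocessing** gives the split: "The dataset will be split into k folds, with 2 folds randomly selected: one for validation and another for testing". The other k-2 folds train the model, and "The number of folds will vary depending on the specific model".
- **Participant Identification and Randomization** describes a step that includes the choice of test data: "A secondary randomization process will be conducted to create k-clusters of data before training the ML algorithm".
- **Timeline** makes the band data repeated: "Passive monitoring will occur continuously for 6 months in both groups", with a further year for the patients with SUD.
- **Data Exclusion** works at day level: "A day with more than 20% of faulty measurements will be excluded from the dataset".
- **Output** defines two duration categories and three relapse categories. By these definitions a patient has one duration label and one relapse label, constant over all his records.
- **Validation and Verification** sets the pass mark at AUC of at least 0.80 and F2 of at least 0.8, and adds: "For model verification, the test dataset will be used to determine final AUC and F2 scores".
- **Blinding** has the one phrase that ties clusters to participants: "the group allocation of participant ID clusters will remain concealed from the second group of researchers".

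**The concern.** The outcome belongs to the man, while the band data belong to the day or the moment. A random partition is sound only if its unit is the man, and neither section that describes the randomisation says so. If daily or time-segmented rows are dealt into folds at random, nearly every man has rows in both training and test. A flexible model can then recognise the man and recall his label. Demographic, childhood-adversity and substance-involvement data, collected only at baseline (Table 1), would act as an identity tag if copied onto each row. Keeping scaling and feature selection inside the training folds would not remove this.

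The AUC and F2 thresholds are the study hypothesis (Principal Findings) and the definition of a fully functional model (Predictive Model). In the Abstract, reaching the AUC threshold leads to the clinical interface. A test AUC that measures recognition of men already seen says nothing about a new patient.

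**Working it through.** **Figure to reproduce.** None. The 0.80 threshold is chosen, not calculated. The minimum of 25 per group is taken from Sample Size as an input.

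**Step 1. No-signal simulation, equal training share in both arms.** Each man gets a random label, and all features are independent of it. Assumptions: 20 band-type features, 60 days per man, k = 5 (three folds for training, one for test), 5-nearest-neighbour classifier, AUC scored per day. There were 20 runs per record-level setting and 100 per participant-level setting; participant-level runs whose test fold held one label only were dropped. The within-person correlation (ICC) was varied because the article gives none.

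| ICC | 25 men, record folds: mean AUC (runs ≥0.80) | 50 men, record folds: mean AUC (runs ≥0.80) |
|---|---|---|
| 0 | 0.50 (0%) | 0.50 (0%) |
| 0.1 | 0.57 (0%) | 0.55 (0%) |
| 0.2 | 0.68 (0%) | 0.62 (0%) |
| 0.3 | 0.82 (70%) | 0.74 (0%) |
| 0.5 | 0.98 (100%) | 0.97 (100%) |
| 0.7 | 1.00 (100%) | 1.00 (100%) |

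With participant-level folds the mean AUC was 0.49 to 0.51 at every ICC. It reached 0.80 in 0% of runs for 50 men and in 0 to 5% for 25 men.

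**Step 2. Constant scores on each row.** With five constant per-man scores added for 25 men, record-level folds gave a mean AUC of 0.78 at ICC 0 (45% of runs passing) and 0.99 at ICC 0.3 (100% passing).

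**Step 3. A second simulation with other settings.** It used 25 men, 10 with the event, 120 days each and ten record-level folds with eight for training.

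- With 15 band features and five constant scores, mean AUC at ICC 0.05, 0.2 and 0.5 was 0.87, 0.94 and 1.00 for a random-feature neural network, and 0.93, 0.99 and 1.00 for 5-nearest-neighbour.
- With 20 band features and no constant scores, the range over both classifiers was 0.53 to 0.55, 0.71 to 0.74 and 0.95 to 0.99.
- Participant-level folds gave 0.48 to 0.54.

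**Step 4. Does F2 protect?** A rule that calls every man positive has recall 1 and precision P (the prevalence), so F2 = 5P/(4P + 1). Setting this to 0.8 gives 5P = 3.2P + 0.8, so P = 0.8/1.8 = 44.4%. At the 60% relapse rate cited in the Introduction, F2 = 3/3.4 = 0.88. Where the positive class is this common, F2 adds little protection.

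**Step 5. What participant folds leave unsolved.** With 25 men and k = 5, a test fold holds 25/5 = 5 men. For 2 versus 3 men there are C(5,2) = 10 equally likely rankings under no signal. Two of them give AUC ≥ 0.80 (5/6 and 6/6), a chance of 2/10 = 20%. For 5 versus 5 it is 19/252 = 7.5%. With one row per man and one test fold, the simulated false-pass rate was about 16% for 25 men and 5% for 50. If all 25 men are scored out of fold (10 versus 15), the null SD of the AUC is √(26/(12 × 10 × 15)) = 0.120. Then z = 0.30/0.120 = 2.5, a chance of about 0.6%. This last figure treats the pooled scores as independent and comparable across folds, so it is approximate.

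**The case against.** A reader might infer that the plan randomises records and not participants. The article does not say that, and several cues point the other way:

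- Blinding speaks of "the group allocation of participant ID clusters will remain concealed from the second group of researchers", and that group trains and tests the models.
- Sample Size counts participants when it applies the neural-network rule.
- Profiles builds phenotypes for individuals, and most questionnaire data exist only once or twice per man.

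With one row per man, the overlap cannot occur. The passage "Data will be clustered time-wise according to the time of the day and the reported activity accordingly" concerns noise from varying activity, not folds, and day-level exclusion is data cleaning. Neither defines a training row.

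It can also be said that a condensed article leaves the grouping variable to the full protocol. That would carry weight if the article were silent on the split. But it sets out the procedure, and the result feeds the pass criterion. The one phrase about ID clusters concerns concealment of group and does not say how folds are formed.

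The objections to the size stand in part. Nearest-neighbour is not a planned classifier, and the random-feature network only stands in for the planned one. The second simulation trained on eight of ten folds at record level but three of five at participant level. F2 was not simulated. The first simulation, with equal training shares, shows the same contrast, but the exact values should not be read as forecasts.

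**Conclusion.** The point holds as an unfixed unit of randomisation in a stated procedure, not as proof that records will be split. If folds are drawn on days or time segments, a no-signal model can reach AUC 0.80. Under the settings used, this happens with band features alone from an ICC of about 0.3 for 25 men and somewhere between 0.3 and 0.5 for 50 men. It can happen at lower ICC when constant baseline scores sit on each row. With band features alone and an ICC of 0.2 or less, mean AUC stayed below 0.80, and with one row per man there is no leak. ICC, days per man, feature count, row layout, k and classifier are all assumptions. The matter deserves correction before training because the AUC threshold decides whether a tool goes into clinical use.

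**What to change.** In Participant Identification and Randomization and in Data Preprocessing, state that folds are formed by participant ID. All records of one man (every day, both psychological assessments, every craving assessment) go to the same fold. Stratify by outcome label, and by group for the model that separates patients from healthy men.

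In Validation and Verification, rotate the test role so that each man is scored once by a model that was neither trained nor tuned on his data. Reduce his records to one score, pool these scores over all men, and report the final AUC and F2 with confidence intervals. Pooling is needed because participant folds alone leave the roughly 20% chance pass of a 2-versus-3 test fold.

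The cost is a few sentences, a grouped partition in the software and more computing. No new data are needed. Results reports that data were still being labelled and preprocessed as of June 2025, so the change is timely if training has not begun. The downside is that the reported AUC will probably be lower and less precise, and rare outcome categories may be too small to appear in every fold.

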Machine learning (ML) has also been used as a tool for the diagnosis of anxiety disorders with the use of speaking patterns, gaming activities, and self-reports [40-49]. It has also allowed researchers to measure the severity and variability of that disorder in varying environments through wearables, allowing remote intervention and through simulations [30,48,50-52]. It has also been used in predictive models for early depression diagnosis through smartphone use, severity, and progression through physical activity, sleep, and social interaction data [53-61]. In addition, ML models (MLM) have been trained to detect relapse in MDD and risk of suicide [62-64]. Similarly, it has been used to predict the start of a psychotic episode 5 days before it by using patterns of movement and sleep disturbance [63,65].

With a 60% relapse rate, an average of 5 recovery attempts required for full remission, and a growing number of new patients with SUD presenting at younger ages [2], this disorder represents a significant opportunity for digital health technologies. These tools, often used in managing cognitive and mood disorders commonly comorbid with SUD, have the potential to enhance treatment effectiveness and reduce relapse rates.

This study aims to integrate physiological, behavioral, and psychological data through digital technologies to develop comprehensive digital profiles of individuals with SUD. These profiles will be analyzed using ML tools to identify clinically relevant patterns. The resulting models are intended to serve as complementary tools in clinical practice, supporting treatment decisions, improving prognostic accuracy, and facilitating the monitoring of patients in remission.

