### Participants and Study Setting

#### Sample Size

The minimum sample size was determined using Epidat 4.2 software (Xunta de Galicia), following the equation for estimating the comparison between independent means. The calculation was based on data reported by Rykov et al [30], in a study where patients were screened using wearable devices, and (MLMs were applied (Textbox 1).

Sample characteristics.Variance: distinctStandardized mean difference=2.54Expected SD of population 1=1.6Expected SD of population 2=3.21Ratio between sample sizes=1CI=95%Statistical power=80%

In addition, based on the rule of one-to-ten for artificial neural network (ANN) models suggested by Kavzoglu and Mather [31], in which a sample should be at least 10-100 times the numbers of independent variables (4 in this study, based on the 4 suggested profiles), a sample of 40-400 participants was obtained. Therefore, a minimum sample size of 25 was determined for each group. Participants will be recruited within 2 years of the beginning of the study, aiming for recruitment greater than 25 per group.

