### Output

The primary objective of this study is to develop a MLM capable of predicting clinical outcomes in patients. To achieve this, the data will be segmented and classified into 5 categories (Figure 5). Around 2 of these categories will correspond to the first layer, which pertains to the duration of the therapeutic process, while the remaining 3 will focus on the latency of relapse, if any.

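### Final AUC and F2 come from one randomly selected test fold with k left open, and at 25 SUD patients that fold may well lack a relapse class

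*Protocol article*

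**What the plan says.** *Data Preprocessing* describes a k-fold approach: "The dataset will be split into k folds, with 2 folds randomly selected: one for validation and another for testing". The other k-2 folds are for training. The same section adds: "The number of folds will vary depending on the specific model". *Participant Identification and Randomization* says how the folds arise: "A secondary randomization process will be conducted to create k-clusters of data before training the ML algorithm", a step that also picks the test data.

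*Output* states that "the data will be segmented and classified into 5 categories": two for the duration of therapy and three for relapse latency (early relapse, late relapse, maintenance). *Validation and Verification* uses the validation data to compare models and the test data for the final AUC and F2, with thresholds of 0.80 and 0.8.

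On size, *Sample Size* says "Therefore, a minimum sample size of 25 was determined for each group", with recruitment "aiming for recruitment greater than 25 per group". Only the SUD patients carry the five outcome labels.

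**The concern.** With about 25 men carrying three relapse labels, a fold holds five men at k=5 and two or three at k=10. No sentence requires every class to appear in the fold that delivers the final figures.

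A one-versus-rest AUC is the share of case/non-case pairs that the model ranks correctly. With no cases there are no pairs and no AUC. F2 equals 5TP/(5TP + 4FN + FP). With no cases TP and FN are both 0, so F2 is 0 if there is any false positive and undefined otherwise.

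The two thresholds decide whether the model counts as fully functional (*Predictive Model*), and the Abstract makes the clinical interface conditional on the AUC. The validation fold, on which models are compared, is exposed in the same way. Both the choice of model and the final verdict could then depend on which men fall into two small folds.

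**Working it through.** **Inputs from the article.** At least 25 SUD patients (*Sample Size*); three relapse and two duration labels (*Output*); "With a 60% relapse rate" (*Introduction*, a background figure). 60% of 25 is 15 relapses, which leaves 10 in maintenance.

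The article gives no figure for fold composition that could be reproduced. I take its 25 as stated. Its inputs, with 2.54 read as a raw difference, give (1.960+0.842)² × (1.6²+3.21²)/2.54² = 15.65, so 16 per group. That mismatch is a separate matter and does not enter below.

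**Assumptions, because the article does not fix them.** k is 5 or 10; the participant is the unit; folds are filled at random without regard to label. Early/late/maintenance is 8/7/10, 10/5/10 or 12/3/10, with 9/8/8 as a near-balanced case.

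**Formula.** For a fold of m men out of N, with class sizes c₁, c₂, c₃:

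P(at least one class absent) = [Σ C(N−cᵢ, m) − Σ C(N−cᵢ−cⱼ, m)] / C(N, m)

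**k=5, m=5, C(25,5)=53,130**
- 10/5/10: (3,003 + 15,504 + 3,003 − 252 − 1 − 252)/53,130 = 21,005/53,130 = 0.395
- 8/7/10: (6,188 + 8,568 + 3,003 − 252 − 21 − 56)/53,130 = 17,430/53,130 = 0.328
- 12/3/10: (1,287 + 26,334 + 3,003 − 252 − 0 − 792)/53,130 = 29,580/53,130 = 0.557
- 9/8/8: (4,368 + 6,188 + 6,188 − 56 − 56 − 126)/53,130 = 16,506/53,130 = 0.311

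By simulation, the test or the validation fold lacks a class with probability 0.55 (8/7/10), 0.65 (10/5/10) and 0.84 (12/3/10).

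**k=10, five folds of three men and five of two.** A three-man fold holds all classes with probability c₁c₂c₃/C(25,3), where C(25,3)=2,300.
- 9/8/8: 1 − 576/2,300 = 0.750
- 8/7/10: 1 − 560/2,300 = 0.757
- 10/5/10: 1 − 500/2,300 = 0.783
- 12/3/10: 1 − 360/2,300 = 0.843

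A two-man fold always lacks a class. Averaged over both fold sizes, the risk is 0.87 to 0.92. From k=9 upward some folds hold only two of 25 men, so this occurs whatever the class split.

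**Larger samples, same proportions**

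| SUD patients | k=5 | k=10 |
|---|---|---|
| 50 (20/10/20) | 0.088 | 0.430 |
| 100 (40/20/40) | 0.007 | 0.104 |

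**Two-class tasks**

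| Task | k=5 | k=10 |
|---|---|---|
| Duration 13/12 | 0.04 | 0.22-0.48 |
| Duration 15/10 | 0.06 | 0.25-0.50 |
| Duration 20/5 | 0.29 | 0.50-0.67 |
| SUD vs control 25/25 | 0.0006 | 0.05 |

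**What stratified folds alone achieve.** At k=5 every fold can hold all three classes for 8/7/10 and 10/5/10. With 12/3/10 at least 2 of 5 folds still lack late relapse. At k=10 at least 3, 5 and 7 of 10 folds lack it for 8/7/10, 10/5/10 and 12/3/10. A five-man fold with one late relapser offers 1 × 4 = 4 pairs. Without ties its AUC can only be 0, 0.25, 0.5, 0.75 or 1, so reaching 0.80 means a perfect ranking.

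**The case against.** A reader might infer that the folds are unstratified. The article does not say so. The random step in *Data Preprocessing* chooses among folds already formed, and stratified assignment is also a randomization. A condensed article may leave that detail to a fuller document. *Limitations and Considerations* even hints at some structure: "Data clustering by groups before final testing introduces a potential risk that research staff may infer group assignments prematurely". In context that means SUD versus control, not outcome class. This objection stands: the probabilities are conditional on random filling.

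A reader might also infer that the criterion cannot be computed at all. That goes too far. F2 is 0, not undefined, when there are false positives, and if folds rotate and predictions are pooled, AUC is computable. *Data Preprocessing* does speak of cross-validation, but it names one fold for testing, and *Validation and Verification* refers to a single test dataset. Rotation is possible but not stated.

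The size of the risk rests on an assumed k, class split and unit. If records rather than men were split, classes would rarely be absent, although *Blinding* speaks of clusters of participant IDs, which points to the participant. The 25 is a floor, and 50 or 100 SUD patients reduce the risk greatly at k=5. Against that, *Withdrawal Criteria* and *Data Exclusion* discard participants, and 18 SUD patients were enrolled by June 2025.

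What remains does not depend on silence about stratification: a single test fold and a k that varies by model are both stated.

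**Conclusion.** The concern holds in limited form. The article fixes one randomly selected fold for validation and one for testing, leaves k to vary by model, and takes the decisive AUC and F2 from the test data, with no requirement that every class be present. At 25 SUD patients and random filling by participant, the test fold lacks a relapse class in about 31-56% of draws at k=5 and about 75-100% at k=10. With 50 SUD patients split 20/10/20 it is about 9% and 43%.

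The effect falls on the relapse layer and on unbalanced duration labels. It does not extend to SUD versus control, nor in any important degree to near-balanced duration labels at k=5. The documents do not support saying that the split is unstratified or that the success rule can never be evaluated. They do support saying that, near the minimum size, the verdict can turn on the draw. The change is worth making before the data are partitioned.

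**What to change.** In *Participant Identification and Randomization* and *Data Preprocessing*, state that:

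- there is one participant-level partition, shared by the duration and relapse layers, so that no man is in training for one layer and in test for the other;
- it is stratified by relapse label, and by duration label where counts allow;
- one modest k is fixed in advance for all models;
- every fold serves once as the test fold, with model choice and tuning done inside the remaining folds;
- AUC and F2 are computed once, from the held-out predictions of all participants.

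Pooling is the essential part, because stratification cannot place a class with fewer than k members in every fold. Capping k at the smallest class count would not be a good substitute. With 12/3/10 it gives k=3, and the k-2 rule then leaves a single training fold of about 8 men.

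The cost is a few sentences, a change to the partitioning code and more computation. The pooled AUC also mixes predictions from models fitted on different training folds, which should be acknowledged when it is reported. No extra data or participants are needed.
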